## Abstract

**Background:**

Attention has shifted to the use of non-pharmacological interventions to prevent cognitive decline as a preventive strategy, as well as for those at risk and those with mild cognitive impairment. Early introduction of psycho-social interventions can address cognitive decline and significantly impact quality of life and the wellbeing of elderly individuals. This pilot study explores the feasibility of using art therapy and music reminiscence activity to improve the cognition of community living elderly with mild cognitive impairment.

**Methods/Design:**

This open-label, interventional study involves a parallel randomized controlled trial design with three arms (two intervention arms and a control group) over a nine-month period. Participants will be community-living elderly individuals aged 60–85 years, both genders, who meet predefined inclusion and exclusion criteria. In the initial three months, interventions will be provided weekly and for the remaining six months fortnightly. A sample size of 90 participants is targeted based on expected neuropsychological test performance, a primary outcome measure, and drop-out rates. The randomization procedure will be carried out via a web-based randomization system. Interventions will be provided by trained staff with a control group not receiving any intervention but continuing life as usual. Assessments will be done at baseline, three months, and nine months, and include neuroimaging to measure cerebral changes and neuropsychological tests to measure for changes in cognition. Secondary outcome measures will include mood changes in anxiety and depression and telomere lengths. Statistical analysis will be undertaken by statisticians; all efficacy analysis will be carried out on an intention-to-treat basis. Primary and secondary outcomes will be modeled using the linear mixed model for repeated measurements and further analysis may be undertaken to adjust for potential confounders.

**Discussion:**

This will be the first study to compare the effectiveness of art therapy and music reminiscence activity in a randomized controlled trial. We expect that the trial will provide useful evidence for developing psychosocial interventions for the elderly with mild cognitive impairment.

**Trial registration:**

The study was registered on 7 July 2016 at Clinical Trials.gov, a service of the US National Institute of Health (NCT02854085), retrospectively.

**Electronic supplementary material:**

The online version of this article (doi:10.1186/s13063-017-2080-7) contains supplementary material, which is available to authorized users.

## Background

Population aging is a global public health concern and dementia is one of the major causes of disability and dependency in the elderly population worldwide [1]. Research now targets the prevention or delay of cognitive decline as a more beneficial approach and attention has shifted to non-pharmacological interventions and preventive strategies for cognitively normal elderly and those exhibiting mild cognitive problems.

Mild cognitive impairment (MCI, DSM-5 Minor Neurocognitive Disorder) [2] is associated with high burden with about 50% of individuals going on to develop dementia within five years. While 14–40% may return to normal cognitive functioning over time, others may exhibit a persistent form of MCI without conversion [3, 4]. Interventions from stimulating leisure activities and an active cognitive lifestyle to address cognitive decline at this stage, have a significant impact on the quality of life and wellbeing of elderly individuals and also illness progression [5]. Evidence suggests that the causes of aging are multifactorial, ranging from increased inflammation and oxidative stress to decreased mitochondrial function, hormonal levels, and genome instability [6]. However, the aging brain still exhibits plasticity which allows interventions and cognitive training to bring about alterations in cerebral morphology and function [7].

A systematic review of psycho-social interventions (69 prospective controlled trials) found positive effects on quality of life and positive mental health [8] and engaging in stimulating activities at least twice a week reduced the risk of dementia by 50% [9]. Interventions focusing mainly on lifestyle modifications, notably the FINGER trial, have reported significant benefits from a multifaceted intervention that included diet, exercise, cognitive training, and vascular monitoring [10].

Our earlier work in an open-label trial of art therapy (AT), music reminiscence, mindfulness practice, and Tai Chi exercise with community-living elderly, revealed improvements in sub-syndromal anxiety and depressive symptoms [11]. This was followed by a randomized controlled trial (RCT) to examine Mindfulness Awareness Practice (the control group received Health Education) in the elderly with MCI and designed with a nine-month duration deemed sufficient for intervention response [12]. Interventions were provided weekly for three months and then monthly for six months and a range of “psychobiomarkers” were investigated [13].

Telomere length was one of those measured as it is widely accepted as a biomarker for cellular aging and cognitive decline with changes from various activities resulting in longer telomeres [14–16]. Preliminary findings from the Mindfulness Awareness Practice RCT have revealed changes in functional brain activity, neuropsychological tests, telomere lengths, and oxidative stress markers after just three months of weekly intervention (manuscript in preparation). Importantly, the frequency of the activity had a significant impact on the sustainability of gains produced by the intervention [17]. Existing research on AT and music reminiscence activity (MRA), however, is limited, especially on the efficacy of these interventions on cognition. Kim has shown that AT improves mood and overall wellbeing of elderly individuals, but the cognitive status of the participants was unknown [18]. While Alders and Levine-Madori have results that seem to suggest that AT is useful in improving cognitive performance [19], the study methodology was not rigorous. The experimental group could choose the activity to participate in and could attend as few as three of the ten AT sessions. The study by Rusted et al. [20] did not clearly explain the control group activity and recruited a wide range of dementia participants. None of the studies have been of sufficient rigor or focused on elderly with MCI.

Listening to music effectively stimulates the auditory cortex and other brain areas related to attention, semantic processing, memory, motor function, and emotional processing [21]. Yet studies on the specific use of MRA and its efficacy for elderly with MCI are rare. Most of the research has examined music therapy, with components of reminiscence, for mood symptoms, where listening to music they preferred [22] and choosing the type of music to listen to reduced anxiety and depression in the elderly [23, 24]. Petrovsky et al. did a review of the utility of music interventions on mood in the elderly with mild dementia and found that many of the studies were not methodologically strong, indicating that the evidence was inconclusive [25].

The research on music therapy and cognitive changes however has shown positive improvements on Mini-Mental State Examination (MMSE) scores, even one month post intervention [24] and on the short-term for working memory and quality of life in elderly with mild or moderate dementia [26]. However, the efficacy of music therapy for cognitive improvement is still debated and there is a gap in the literature for music reminiscence activities in elderly with MCI.

## Methods/Design

### Aims of study

This pilot study aims to explore the feasibility of using AT and MRA to improve the cognition of community living elderly with MCI (Diagnostic and Statistical Manual-5: Mild Neurocognitive Disorder) [2].

The primary outcomes will be the structural cerebral changes that occur with the two interventions and the extent to which the therapies may reverse cognitive impairment and/or prevent further cognitive decline on neuropsychological tests of cognition. This will be based on participants’ pre-, three-month and nine-month neuropsychological test scores, compared with individuals in the control arm who do not participate in active interventions.

Secondary outcomes comprise changes in blood biomarkers, psychological wellbeing, and mood symptoms.

We hypothesize that participants in both active intervention arms will have (1) improved functional connectivity, (2) improved neuropsychological cognitive test scores, (3) increased telomere lengths, and (4) enhanced psychological wellbeing and reductions in anxiety and depressive symptoms compared with the control group.

No a priori hypotheses were developed as to whether AT or MRA is more effective as the comparison is exploratory.

### Study design

This is an open-label, interventional study involving a parallel RCT design with three arms and run over nine months. The duration of nine months was used in previous RCTs of psychosocial interventions at our center and provided a trial length of sufficient duration which yielded measurable changes. The protocol was prepared according to the Standard Protocol Items: Recommendations for Interventional Trials (SPIRIT) guidelines (see Fig. 1, Additional file 1, and Fig. 2). Interventions will be weekly for the first three months, then fortnightly for the remaining six months. Weekly interventions provide greater practice effects and improvements in cognition and brain function, if any, can be detected by three months. In the subsequent six months, the frequency of the interventions has been increased to fortnightly, based on previous trial experience that monthly interventions do not sustain the early gains. Study evaluations will be done by comparing the two intervention groups (AT and MRA) and a control group. Participants will have written informed consent taken, screening, and baseline measures completed before randomization into one of the three study arms.

**Fig. 1 Fig1:**
[figure not shown]
Workflow plan for participants

**Fig. 2 Fig2:**
[figure not shown]
Standard Protocol Items: Recommendation for Interventional Trials (SPIRIT) figure: the schedule of enrolment, interventions, and assessments. *M* months, *VAS* visual analog scale, *ADL* Barthel Index (Activities of Daily Living), *iADL* instrumental Activities of Daily Living, *PDQ* Perceived Deficits Questionnaire, *MMSE* Mini-Mental State Examination, *CDR* Clinical Dementia Rating, *GDS-15* Geriatric Depression Scale (15-item), *GAI-20* Geriatric Anxiety Inventory, *fMRI* functional magnetic resonance imaging, *ZBI* Zarit Burden Inventory

Intervention Arm 1: Participants will receive AT

Intervention Arm 2: Participants will receive MRA

Control Arm: Participants will not receive any intervention but continue their life as usual.

### Eligibility criteria

The inclusion criteria are:Aged 60–85 years, both genders, and living in the community and fulfils the operational definition/criteria of MCI: (a) at least one age-education adjusted neuropsychological test Z score < −1.5; (b) do not meet DSM V criteria for a major neurocognitive disorder; (c) memory/cognitive complaint preferably corroborated by a reliable informant;Functions independently as assessed with Barthel’s Activities of Daily Living and instrumental Activities of Daily Living;Able to travel to the data collection site on their own and participate in the activity weekly for 12 weeks and then fortnightly for six months.

The exclusion criteria are:Those who do not meet the above inclusion criteria (i.e. do not have MCI diagnosis);Those with dementia/major neurocognitive disorder or normal aging;Presence of a neurological condition, e.g. epilepsy, Parkinson’s disease, stroke;Presence of a major psychiatric disorder, e.g. major depression, psychoses;Terminal illness, e.g. cancer;Presence of significant visual and/or hearing impairment and color blindness;Participants in another intervention study at the same time.

### Randomization procedure

Participants will be randomized (on the same day after taking written informed consent, screening, and completing baseline measures) to the AT, MRA, or control groups at a 1:1:1 allocation ratio. Balanced intervention assignments will be achieved using permuted block randomization stratified by gender. Block size will be determined by the statistician responsible for generating the randomization list and will not be made known to the clinical investigator or site personnel.

Implementation of the randomization process will be carried out via a web-based randomization system by Singapore Clinical Research Institute. The randomization system will then determine the intervention arm and provide a unique participation number to be used for the participant.

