#### Baseline

Demography questionnaire, basic health screen, functional assessment, neuropsychological tests, neuroimaging, and blood investigations are carried out.

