#### Nine months (study end)

Basic health screen (excluding height), functional assessment, neuropsychological tests, and blood investigations are repeated.

The time taken for the health screening, completion of the demographic data, main questionnaire, and blood sample collection will take about 1 h.

The neuropsychological tests will take about 1 h 45 min. The baseline visit to TaRA@JP will take about 3 h. Subsequent visits at three months and nine months will take 2 h.

The fMRI scans will be conducted at CIRC in NUS and the appointment will be on another day. The imaging sessions will take 1 h. However, the time within the scanner is about 45 min.

See Tables 1 and 2 for the visit schedules for the interventions and control groups, respectively.

**Table 1 Tab1:** Visit schedule for intervention arms

Pre-baseline/Baseline	Three months	Nine months (study end)
Informed consent process	Main questionnaire	Main questionnaire
Eligibility screening	Neuropsychological tests	Neuropsychological tests
Demographic data	MRI scan	Clinical Dementia Rating
Main questionnaire	Weight, vital Signs	Weight, vital signs
Neuropsychological tests	Blood sample collection	Blood sample collection
Clinical Dementia Rating		
MRI scan		
Basic health screen		
Blood sample collection

**Table 2 Tab2:** Visit schedule for controls

Pre-baseline/Baseline	Three months	Nine months (study end)
Informed consent process	Main questionnaire	Main questionnaire
Eligibility screening	Neuropsychological tests	Neuropsychological tests
Main questionnaire	MRI scan	Clinical Dementia Rating
Demographic data	Weight, vital signs	Weight, vital signs
Neuropsychological tests		Blood sample collection
Clinical Dementia Rating		
MRI scan		
Basic health screen		
Blood sample collection		

Blood samples (3 mL) will be collected at three time-points for those in the AT and MRA arms (baseline, three months, nine months) for telomere lengths. For the control group, it will be done twice, at baseline and at nine months.

Samples will be stored immediately in a mini-fridge (4 °C) at TaRA@JP and transported within 12 h of collection to the labs.

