### Data management

Data forms will be coded with a study number (starting with 001). Data will be entered and stored on a standalone computer and the information will be password protected. Only the principal investigator, investigators, and study coordinator in the project will have access to the data for analysis. In accordance with NUS data management policy (DPRT-2011-04), data will be kept for ten years after the research is completed and all data (electronic and hard copy) will be destroyed after the storage period.

The investigators and the trial coordinators will monitor that the informed consent process is conducted appropriately and that informed consent was obtained prior to proceeding with any study procedures. Only participants who meet study eligibility criteria will be enrolled.

Participants’ data will be identified only by a study number. Only the principal investigator will have access to identifiers that can link the data to the individual participant. De-identified data will be collected and analyzed as specified in the protocol. Participants who drop out will be noted and their reasons documented. Primary and secondary end-points will be reviewed to ensure data are correctly entered and meet protocol requirements.

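### The protocol contradicts itself on whether the baseline MRI comes before randomisation; if the same-day rule is followed, the scan falls after open-label allocation

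*Protocol article*

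**What the plan says.** All references are to the protocol article.

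- **Randomization procedure:** "Participants will be randomized (on the same day after taking written informed consent, screening, and completing baseline measures", with 1:1:1 allocation to art therapy, music reminiscence or control.
- **Study design:** the trial is open-label, and participants have "screening, and baseline measures completed before randomization into one of the three study arms".
- **Baseline** (under Assessments and visit schedule): "Demography questionnaire, basic health screen, functional assessment, neuropsychological tests, neuroimaging, and blood investigations are carried out". Tables 1 and 2 also place the MRI in the pre-baseline/baseline column for all arms.
- **Nine months (study end)**, where visit logistics are described: "The fMRI scans will be conducted at CIRC in NUS and the appointment will be on another day". The same section says "The baseline visit to TaRA@JP will take about 3 h".
- **Data management:** the investigators and coordinators check that "informed consent was obtained prior to proceeding with any study procedures".
- **Outcomes** lists change in cerebral functioning at three months as primary, and **Aims of study** names structural cerebral change as primary. **Statistical analyses** places cerebral functioning among the secondary outcomes and analyses it in the same way as the primary ones, through change from baseline.

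**The concern.** The order of baseline measurement and allocation is a basic protection in a randomised trial. Here the text gives two incompatible orders for one measurement, the baseline scan.

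If the scan follows allocation, two things can go wrong. First, the scan is a separate appointment at another site, and Risks and safety monitoring itself expects that some people will find it uncomfortable or ask to stop. In an open-label trial with a no-intervention control, willingness to attend may depend on the arm once it is known, so the participants with a baseline scan may no longer be comparable across arms. Second, if sessions begin before the scan, the baseline in the two active arms may already contain some response.

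Imaging is scheduled only at baseline and three months, so the baseline scan enters every observed imaging change and no later scan can replace it.

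**Working it through.** This is a question of sequence, so the check is to put the statements in order and see whether one timetable satisfies them all.

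1. **Day of randomisation.** Randomization procedure names consent, screening, baseline measures and randomisation together under one same-day phrase. Call this day D.
2. **What must be done by then.** Study design and Randomization procedure both put baseline measures before randomisation. The Baseline section and Tables 1 and 2 make the MRI one of those measures. So the MRI must be done on or before D.
3. **Where the scan falls.** The visit schedule puts the scan on a different day from the visit to the research centre. So the MRI is not on D.
4. **Can it be earlier than D?** Data management requires consent before any study procedure, and consent is taken on D. So the MRI is not before D.
5. **Result.** Steps 3 and 4 place the MRI after D; step 2 requires it on or before D. The statements are inconsistent. Keeping the same-day rule puts the scan after allocation.

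**Consistency check on visit times** (all from the visit schedule):

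- Health screen, questionnaires and blood: about 1 h = 60 min.
- Neuropsychological tests: about 1 h 45 min = 105 min.
- Sum: 60 + 105 = 165 min, against a stated baseline visit of about 3 h = 180 min.
- Adding the 1 h imaging session: 165 + 60 = 225 min, which exceeds 180 min.

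The stated times therefore fit a single visit containing everything except the scan. This also shows which baselines are safe: the neuropsychological tests, the questionnaires and the blood sample fit within the visit and can be finished before randomisation on the same day.

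**Who is exposed.** All 90 planned participants (30 per arm) come under the unclear rule. Differential attendance could involve any arm. Contamination of the baseline by treatment could involve at most 30 + 30 = 60 scans, because the 30 controls have no sessions. The text gives no interval between randomisation, scan and first session, so neither effect can be given a size.

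**The case against.** The strongest reply is that no sentence says the scan follows allocation. Study design, Randomization procedure and Baseline all say or imply the opposite order, and the same-day phrase could be read as the day on which the last baseline measure, including the MRI, is finished. The Pre-baseline section describes a separate screening stage with a psychiatric interview for some people, so a single-day sequence is not certain. Figures 1 and 2 (workflow and schedule) were not available in the text examined and may show the intended order.

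This stands in part. It means that a post-allocation baseline scan is not established as fact. It does not remove the contradiction: the same-day phrase covers consent as well as baseline measures, and the softer reading works only if consent and randomisation fall on different days. Staff at the centre cannot tell from the text whether to randomise at the end of the visit or wait for the scan.

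Further points limit the weight of the concern, and they stand:

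- The scan is task-free, so knowing the arm leaves little room for an effect through effort. The main route to bias is attendance.
- A reader might infer that anyone without a baseline scan is lost to the intention-to-treat analysis. The text does not support that. Statistical analyses models baseline and follow-up values together in a linear mixed model, so a person with only a three-month scan can still contribute, although no change is observed for that person.
- The sample size rests on neuropsychological scores, and the study is described as a pilot.

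**Conclusion.** The contradiction is real and needs to be resolved. What follows is conditional: if the same-day rule is applied as written, the baseline of an imaging outcome listed as primary under Outcomes (secondary under Statistical analyses) is taken after open-label allocation. Attendance can then differ by arm, and no text shown rules out a scan after the first session in the active arms.

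Two stronger readings are tempting and should not be drawn. One is that baseline scans were in fact taken after allocation; the document does not say so. The other is a numerical dilution of the effect. If response accrued linearly over the 12 weekly sessions, a scan taken after k sessions would remove k/12 of it (1/12 = 8%, 2/12 = 17%, 4/12 = 33%). But both the linearity and any value of k are assumptions. A scan after allocation but before session 1 has k = 0 and no dilution, and the controls cannot be diluted at all.

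The size of any bias is therefore unknown. The problem is confined to imaging.

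**What to change.** **Protocol text.** Reconcile Study design, Randomization procedure, Baseline and the visit-schedule paragraph. Delete the same-day phrase. State that the web-based system releases an allocation only after the baseline MRI and the other baseline measures are recorded, and that sessions start after that.

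**Participants already randomised.** Trial status gives recruitment from 13 June 2016 and a trial end in April 2017. With nine months of follow-up, the last randomisation would be about July 2016, so a change to the system may come too late for many. For these participants:

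- record the date of the baseline scan relative to allocation and to the first session;
- report missing baseline scans by arm;
- run a sensitivity analysis of the imaging outcome limited to scans taken before the first session and, where numbers allow, to scans taken before allocation.

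These steps show how far the problem occurred. They cannot fully restore a pre-randomisation baseline.

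**Cost.** A short amendment and one check in the randomisation system; a few days between consent and allocation; and a few people lost before randomisation. For those already enrolled, the cost is some date extraction and one additional analysis.
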